### Methods against bias

Eligibility assessment, obtaining informed consent and enrolling the participants in the trials are performed at each trial site by one of the local investigators. Institutions will be randomised to start with either the intervention group or the TAU control group. The institutions will be randomised in fully eligible groups (group size of four to eight participants), stratified by site using a centralised web-based tool (http://www.randomizer.at [14 Jan 2013], Medical University of Graz, IMBI, Statistics and Documentation, c/o [name]). The randomisation tool is supervised by the IMBI at the University of Heidelberg, Germany.

Screening and baseline assessment are performed before the randomisation procedure, so that data obtained at intake are blinded with regard to group membership. Furthermore, all interviews will be conducted with someone who is not involved in the training.

To ensure that START NOW is implemented in all residential institutions in a comparable way, all staff trainers are trained before the beginning of the study and have to pass a practical and written test. The 2-day-long pre-training will be conducted after randomisation and before the start of the intervention. To increase treatment adherence, a facilitator manual with a detailed session-by-session outline will be used next to the workbook for adolescents. The application of the modularised sessions is strictly monitored. In addition, trainers are supervised by START NOW facilitators every other week during the intervention period. To assess adherence and competence, two training sessions of the programme (one in unit 1, one in unit 2) will be either directly attended by one START NOW supervisor or videotaped. The quality check (Quality Assurance Form [QAF] [19]) will be focused on adherence to the content of the programme and basic trainer competencies (use of motivation interviewing, rolling with resistance, validation).

With regard to the trial design, institutions that were randomised to start with the intervention condition first and subsequently provide a second cycle of TAU have to fulfil two conditions to eliminate potential carry-over effects:Only social workers are involved who have not been previously trained and an exchange on START NOW content between girls is unlikely because of rare opportunity.In case girls who participated in START NOW remain in the institution in the same living group after the whole cycle has ended, the time interval between the end of an intervention group and a second cycle of TAU is longer than 6 months.

Data quality is continuously monitored by the data management team (IMBI), University of Heidelberg, and the KKS). Data will be entered electronically at each local study centre site. Range checks for data values are done to promote data quality. Clinical monitors inspect subject-related data during on-site visits to ensure that all data are correct, complete and gathered according to data protection laws.

The original study forms will be kept at the trial site. Participants’ files are stored in locked cabinets, and access to the study data will be restricted. Data will be collected, processed and stored according to the data protection laws.

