**Methods/design:**

The study is a prospective, confirmatory, cluster-randomised, parallel-group, multi-centre, randomised controlled trial with 128 institutionalised female adolescents who fulfil the diagnostic criteria of ODD and/or CD. Institutions/wards will be randomised either to provide the 12-week skills training as an add-on intervention or to provide treatment as usual. Once the first cycle is completed, each institution will run a second cycle with the opposite condition. Primary endpoints are the pre-post change in number of CD/ODD symptoms as assessed by a standardised, semi-structured psychiatric interview (Kiddie Schedule for Affective Disorders and Schizophrenia for School-Age Children–Present and Lifetime, CD/ODD section) between baseline and the end of intervention, as well as between baseline and a 3-month follow-up point. Secondary objectives include pre-post change in CD/ODD-related outcome measures, most notably emotional regulation on a behavioural and neurobiological level after completion of START NOW compared with treatment as usual.

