## Methods/design

The present study is a prospective, confirmatory, cluster-randomised, multi-centre, international phase III trial with two parallel groups (intervention vs. TAU) and three trial phases (baseline assessment, 12 weeks of treatment, 12 [±1] weeks of follow-up observation). The intervention condition is incorporated into the usual standard care within residential care (START NOW + TAU) vs. TAU. A randomised controlled AB-BA design will be used. Institutions will be randomised to start either with the intervention group (A) or with the control group (B) (TAU). After having conducted A or B, each institution will run the other condition: Institutions starting with TAU receive START NOW, and institutions that finished START NOW and the follow-up assessment conduct a new group with TAU, whereby strict rules are defined to eliminate the risk of carry-over effects.

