### Limitations

A limitation of this study lies in the fact that a blind assessment can be realised only during baseline assessment. At post-assessment and follow-up, participants and other informants included in the assessments (social workers and adolescents) are aware of the condition they are in, and thus their evaluation may be biased. However, to overcome potential bias with regard to the primary outcome measure, the interview assessing CD/ODD symptoms will be conducted with social workers who are not involved in the training. In addition, to assess main secondary measures of emotion processing, objective neurobiological indicators are used which are not influenced by expectation effects.

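### The claim of concealed intake and a blind baseline can hold only for the first cycle, because each institution's second-cycle condition is fixed in advance

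*Protocol article*

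**What the plan says.** **What is randomised.** Methods against bias: "Institutions will be randomised to start with either the intervention group or the TAU control group". The Abstract then says "Once the first cycle is completed, each institution will run a second cycle with the opposite condition", and the opening of Methods/design says "After having conducted A or B, each institution will run the other condition". No second randomisation is described.

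**Who is in cycle 2.** For institutions that began with START NOW, Methods/design says that "institutions that finished START NOW and the follow-up assessment conduct a new group with TAU". If former participants stay in the same living group, Methods against bias also requires that "the time interval between the end of an intervention group and a second cycle of TAU is longer than 6 months".

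**Who recruits.** The section Methods against bias gives this task to site staff: "Eligibility assessment, obtaining informed consent and enrolling the participants in the trials are performed at each trial site by one of the local investigators".

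**What is claimed about intake.** Methods against bias: "Screening and baseline assessment are performed before the randomisation procedure, so that data obtained at intake are blinded with regard to group membership". Limitations says that "a blind assessment can be realised only during baseline assessment". Neither statement is restricted to a cycle.

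**What the baseline feeds.** Under Statistical methods, the primary endpoint is the change in ODD/CD score from baseline, and the baseline symptom count is also a covariate. Under Primary outcome measure, K-SADS-PL ratings rest on all sources of information together with clinical judgement.

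**The concern.** The blind-intake claim depends on an order of events: intake first, allocation second. In cycle 2 that order is reversed. The institution's only randomisation has already taken place, and its result determines the second condition.

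Two biases become possible, and randomising the order of conditions removes neither.

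- **Recruitment bias.** Which girls are approached, judged eligible and agree to take part may depend on the coming condition.
- **Baseline-rating bias.** A symptom count that involves clinical judgement may be rated with the coming condition in mind. That count enters the primary change score directly.

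The article already concedes that the post-treatment and follow-up informants know their condition. Blind intake is therefore a main remaining protection for the primary outcome, in a trial described as confirmatory. A reader would take it to cover the whole sample.

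**Working it through.** **1. Order of events**

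| Step | Cycle 1 | Cycle 2 |
|---|---|---|
| Condition determined | at randomisation, after intake | at the cycle-1 randomisation |
| Screening, consent, baseline | before randomisation | after it; for START NOW-first institutions, after the first group's follow-up |
| Condition foreseeable at intake? | no | yes, to the institution and local investigators |
| Masking of recruiters or baseline interviewers to the institution's order | not needed | none described |

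The stated safeguards are interviews with people not involved in the training, untrained social workers and a time gap. They address informant involvement and carry-over, not foreknowledge at intake.

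**2. The plan's own sample size.** Inputs from Sample size calculation and statistical analysis: difference 3 − 1 = 2, SD 3.5, two-sided 5%, power 80%, design effect 1.08, drop-out 15%. The two-sample t test needs 49.05 per arm, rounded up to 50. Then 2 × 50 × 1.08 = 108, and 108 / 0.85 = 127.1, rounded up to 128. Both figures reproduce. The design effect implies a mean group size of 1 + 0.08 / 0.02 = 5.

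**3. Share of the sample in cycle 2.** The article does not give it. All rows assume that both cycles count towards the 128.

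| Assumption | Share | Girls of 128 |
|---|---|---|
| All institutions run both cycles, equal groups | 50% | 64 |
| Group sizes 8 then 4 (limits of the stated range) | 4/12 = 33% | 43 |
| Group sizes 4 then 8 | 8/12 = 67% | 85 |
| 75% of institutions complete cycle 2 | 0.75/1.75 = 43% | 55 |
| 50% complete | 0.5/1.5 = 33% | 43 |
| 25% complete | 0.25/1.25 = 20% | 26 |

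**4. Illustration of the bias.** Assume that baselines in cycle-2 START NOW groups are rated *d* symptoms too high, and that a share *s* of the START NOW arm is in cycle 2.

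- Unadjusted difference in change: shift = *s* × *d*. With *s* = 0.5 and *d* = 1, this is 0.5, or 0.5 / 2 = 25% of the planned difference.
- Baseline-adjusted, with slope *b* of post-treatment score on baseline: shift = *s* × *d* − (1 − *b*) × *s* × *d* = *b* × *s* × *d*. With *b* = 0.5 (assumed), this is 0.25, or 12.5%.
- Across *s* = 0.20 to 0.67 with *d* = 1: 0.20 to 0.67 unadjusted, and 0.10 to 0.33 adjusted with *b* = 0.5.

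Neither *d* nor *b* comes from the article.

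**5. Precision of a cycle-1-only estimate.** Assume half of the 108 analysed girls, 27 per arm.

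- All data: SE = 3.5 × √(1.08 × 2/54) = 0.70, power 0.81.
- Cycle 1 only: SE = 3.5 × √(1.08 × 2/27) = 0.99. Power at a difference of 2 is 0.51 with 52 individual-level degrees of freedom. With about 54 / 5 ≈ 11 groups, hence about 9 cluster-level degrees of freedom, it is 0.44.

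**6. Which model can give that estimate.** Statistical methods first lists site as a fixed factor, then institution in the model for both hypotheses. In cycle 1 each institution supplies one condition only, so condition is a linear combination of the institution indicators and its effect is not estimable. With site as fixed factor and cluster as random factor, it is estimable. A condition-by-cycle interaction is no substitute: in an AB-BA design it coincides with sequence. A check of the design matrix with institution fixed showed that adding the interaction does not raise the rank.

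**The case against.** The strongest reply accepts that the sentence cannot be literally true of a newly formed cycle-2 group, but holds that the consequences are easily overstated. Much of that stands.

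- **Who knows.** A reader might infer that girls, guardians and every interviewer know the cycle-2 condition. The article does not say so. It supports only that the condition is foreseeable to the institution and local investigators and that no masking is described.
- **How many.** A reader might take half the sample as fact. No section splits the 128 by cycle. Safety and ethical issues also says that the control group later undergoes the intervention, so some cycle-2 START NOW girls may be former controls rather than new recruits. That would weaken the recruitment argument for them.
- **Contamination.** A reader might add that cycle-2 TAU girls are separated from START NOW graduates by a waiting time alone. Methods against bias requires more: social workers without prior training, little opportunity for exchange between girls, and the gap where graduates remain in the living group. Whether this suffices is a separate question and not part of this point.
- **Analyses by cycle.** These are commonly left to the analysis plan, so their absence from an article is no fault. They appear below only as part of the remedy.
- **Timing.** The first group was randomised in January 2015 and recruitment was expected to end by January 2017, so few intakes may remain to be changed.

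None of this makes the unrestricted statement correct.

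**Conclusion.** The concern holds in limited form. The blind-intake statement in Methods against bias, and its repetition in Limitations, are wrong as written for cycle 2, because the condition there was settled by a randomisation that preceded intake. This conclusion follows from the text and needs no numerical assumption.

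The size does rest on assumptions. The affected share is about half under the simplest reading and roughly 20% to 67% otherwise. The shift of 0.25 to 0.5 symptoms, 12.5% to 25% of the planned difference, depends on an invented one-symptom inflation, half the sample in cycle 2 and, for the lower value, an assumed slope of 0.5. It shows what a modest bias could do. It is not evidence that bias occurred, and the article does not support concluding that cycle-2 data are in fact biased or that every baseline there was rated unblinded.

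**What to change.** 1. In Methods against bias and Limitations, restrict the concealment and blind-baseline statements to cycle 1, and add to Limitations that cycle-2 allocation is foreseeable at recruitment and baseline.
2. Pre-specify a cycle-1-only estimate as a supportive analysis, with site (not institution) as fixed factor and cluster as random factor. State its low precision: SE about 0.99 against 0.70, power about 50% or less. It does not replace the primary analysis.
3. Report baseline K-SADS-PL counts and participant characteristics by condition within each cycle.
4. For any remaining cycle-2 intakes, list and approach all eligible girls, and use an existing interviewer who has not been told the institution's order.
5. Do not rely on a condition-by-cycle interaction test: it is aliased with sequence and not estimable with institution fixed.

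The cost is wording, one supportive model, a few tables and some reallocation of existing interviewers. No extra participants are needed. The drawback is that the supportive estimate is too imprecise to settle the matter alone, and step 4 helps only intakes that have not yet taken place.

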### The present study

Within the framework of the FP7 project Neurobiology and Treatment of Adolescent Female Conduct Disorder: The Central Role of Emotion Processing (FemNAT-CD; see http://www.femnat-cd.eu/ for more information), a European multi-disciplinary study, the aim of the present study is to evaluate the effects of an adapted, gender-specific START NOW intervention for females with ODD/CD living in youth welfare institutions. To our knowledge, no prior study has evaluated the effects of such a CBT-based intervention combining aspects of multiple other therapeutic approaches for this specific population in the youth welfare sector. The adaptation of the original START NOW intervention still employs the same underlying principal components of the skills training, but it uses a slightly modified framework (i.e., individual sessions on top of group sessions to enhance personal understanding and relevance of content; shortened length of the programme due to frequent temporary, time-constrained placements) and adjusted content (i.e., illustrations and theme stories tailored to teenage girls’ interests). Furthermore, the intervention will be conducted by staff members of the respective youth welfare institution. Intensive pre-training and supervision, including fidelity monitoring, will be provided. The intervention comprises weekly group sessions (14 sessions, 90 minutes each) and individual sessions (45 minutes each). The aim of the individual sessions is to ensure the transfer of the content of the group training into the personal, daily routines of the participants. Girls are encouraged to practice the skills introduced during the START NOW training between sessions in their daily social interactions with the aid of the responsible social worker. In addition, parents will be sent information on START NOW and information regarding efficient parenting strategies and communication skills with adolescents. In essence, key aspects of the START NOW skills training have remained the same within the adapted version and are well-suited for the target population that can, similarly to the target population of the original format, be described by emotional regulation deficits, many invalidating and traumatic relationship experiences, high impulsivity and a low motivation for change.

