### Primary outcome measure

The primary outcome variable is defined as change in number of fulfilled CD/ODD diagnostic criteria as assessed by a standardised, semi-structured clinical interview between baseline and post-treatment and between baseline and follow-up. The K-SADS-PL will be used [72, 73]. Interviewers will be trained by an experienced clinician, and regular consensus meetings will be held. The K-SADS-PL is a widely used and validated semi-structured diagnostic interview designed to assess current and past episodes of psychopathology in children and adolescents according to DSM-IV-TR/DSM-5 criteria. Interviews are conducted with the adolescent as well as with a social worker from the participant’s respective youth welfare institution who is not involved in the intervention. Symptom measures, diagnoses and severity ratings derived from the interview are based on the obtained information combined with clinical judgement. Thus, summary ratings are achieved by including all sources of information.

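### The two stated times for staff training conflict, and neither keeps staff in TAU-first institutions untrained during their TAU cycle

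*Protocol article*

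**What the plan says.** All points are in the protocol article.

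- **Sequence (Methods/design).** Institutions are randomised to begin with START NOW or with TAU and later switch to the alternative. The article puts it this way: "Institutions starting with TAU receive START NOW, and institutions that finished START NOW and the follow-up assessment conduct a new group with TAU". The same section promises safeguards: "whereby strict rules are defined to eliminate the risk of carry-over effects".
- **Who delivers START NOW (The present study).** "the intervention will be conducted by staff members of the respective youth welfare institution".
- **When they are trained (Methods against bias).** One sentence says "all staff trainers are trained before the beginning of the study and have to pass a practical and written test". The next says "The 2-day-long pre-training will be conducted after randomisation and before the start of the intervention".
- **Carry-over conditions (Methods against bias).** These are addressed to one sequence only: "institutions that were randomised to start with the intervention condition first and subsequently provide a second cycle of TAU have to fulfil two conditions". The condition on staff reads "Only social workers are involved who have not been previously trained". The other condition concerns the interval before the TAU cycle when former START NOW girls stay in the same living group.
- **Informant for the primary outcome (Primary outcome measure).** The second interviewee is "a social worker from the participant’s respective youth welfare institution who is not involved in the intervention".

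**The concern.** The carry-over conditions show that the protocol itself regards START NOW-trained social workers around TAU girls as a threat to the comparison. That threat does not depend on the order of the conditions. In a TAU-first institution, staff who will later run START NOW could have been trained before or during the TAU cycle, and no stated rule prevents this.

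The trained competencies listed under Methods against bias include motivational interviewing and validation, which can be used in everyday care without running a single START NOW session. If such staff work with first-cycle TAU girls, part of the intervention reaches the control arm and the START NOW versus TAU difference shrinks. Both confirmatory hypotheses are exposed: change from baseline to end of intervention (T3) and, if that is rejected, change from baseline to follow-up (T4).

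**Working it through.** **Step 1. The two timing sentences.** Methods against bias places screening and baseline before randomisation. Training before the study begins and training after randomisation are therefore different times on any ordinary reading.

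**Step 2. Each sentence applied to a TAU-first institution.** Randomisation decides which condition an institution starts with, so it precedes the TAU cycle.

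| Rule | START NOW-first institution | TAU-first institution |
|---|---|---|
| Trained before the study begins | Before START NOW | Before the TAU cycle |
| Trained after randomisation, before the intervention | Before START NOW | Any time before the later START NOW cycle: during TAU, or after it |
| Only untrained social workers in the TAU cycle | Applies | Not stated to apply |

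Taken literally, the first rule puts training ahead of TAU. The second allows it during TAU and equally allows it afterwards. The third, which would close the gap, covers only the other sequence.

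**Step 3. Other safeguards.** The rule on the interviewed social worker governs who reports symptoms. It does not govern who cares for the girls.

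**Step 4. The plan's own sample size.** Inputs from Sample size calculation and statistical analysis: difference 3 − 1 = 2, SD 3.5, two-sided α 5%, power 80%, intra-group correlation 0.02, design effect 1.08, drop-out 15%.

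- Two-sample t test (noncentral t): 50 per arm, 100 in total.
- Design effect: 1 + (5 − 1) × 0.02 = 1.08, so the stated figure corresponds to groups of 5. Then 100 × 1.08 = 108, as stated.
- Drop-out: 108 / 0.85 = 127.1, which becomes 128 for equal arms, as stated.

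The stated figures reproduce, and this point does not change them.

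**Step 5. Illustration of dilution.** Assumptions that are not in the document: half of the TAU girls are in TAU-first institutions, all of those institutions train early, and the girls concerned receive a fraction f of the 2-point effect.

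- Expected difference: 2 − 0.5 × f × 2 = 2 − f.
- Effective size: 108 / 1.08 = 100, or 50 per arm.
- Noncentrality: difference / (3.5 × √(2/50)) = difference / 0.7, with 98 degrees of freedom.

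| f | Difference | Noncentrality | Power |
|---|---|---|---|
| 0 | 2.00 | 2.86 | 0.81 |
| 0.10 | 1.90 | 2.71 | 0.77 |
| 0.20 | 1.80 | 2.57 | 0.72 |
| 0.25 | 1.75 | 2.50 | 0.70 |

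The planned margin over 80% is thin, so even f = 0.10 takes power below target. None of these values of f is supported by data in the document.

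**The case against.** The strongest reply is that the second timing sentence is the more specific one and ties the course to the intervention. In a TAU-first institution the intervention is the later START NOW cycle, so a course held just before that cycle fits the text. Carry-over in the usual sense also runs from an earlier condition to a later one, and no START NOW has been delivered before TAU in these institutions. The full protocol and operating procedures, which are not shown, may settle the scheduling.

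Much of this stands. A reader might infer that first-cycle TAU girls will in fact be cared for by trained staff; the document does not support that, because training after the TAU cycle is equally compatible with it. A reader might also assume that everyone around the girls is trained. The text speaks only of the staff who run the groups, and gives neither their number nor whether they work with the TAU girls. Nor does it support a large power loss. A fraction of one half would give a difference of 1.5 and power of about 0.56, but that would credit a 2-day course with half the added effect of 14 group and 12 individual sessions. The article gives no split of girls by sequence, and it plans no analysis restricted to the first cycle that could be said to be undermined. Finally, dilution of this kind works against the intervention and would not create a spurious benefit.

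The reply does not remove the conflict. The article states the timing twice, differently, and expressly confines the untrained-staff condition to one sequence. That is more than detail left out for brevity: followed as written, the first timing sentence produces the exposure that the carry-over condition is meant to prevent.

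**Conclusion.** The point holds as a defect in stated rules, not as evidence that contamination occurs. The two training times must be reconciled, and neither protects the TAU cycle in TAU-first institutions. Any resulting bias would be towards no effect, and its size cannot be derived from the document. The fall in power from about 81% to between 77% and 70% is illustrative and depends on the assumed half split, early training in every TAU-first institution, and f between 0.10 and 0.25. The correction is worth making because it is cheap and because the protocol already accepts the principle for the other sequence.

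**What to change.** - Delete the clause in the first timing sentence that ties training to the start of the study, so that one rule remains.
- Apply the untrained-staff condition to every TAU cycle, whichever condition came first.
- In TAU-first institutions, hold the course only after the outcome assessments of the TAU cycle: after T3 at the least, which protects the first hypothesis, and after T4 to protect the second as well. Where that is not feasible, ensure that staff trained earlier are not involved with the TAU girls until then.
- Record the training date for each institution. Trial status reports the first randomisation in January 2015, so for groups already run the dates would show any overlap with a TAU cycle.

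The cost is wording and the rescheduling of a 2-day course that is planned anyway, with no extra participants or measurements. The downside is that training, and possibly the START NOW cycle, starts later in TAU-first institutions. Waiting for T4 costs more time than waiting for T3, which matters because the article describes placements as often temporary.
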